## Abstract

**Background:**

Drug-related mortality in the United States continues to transform, marked by a surge in overdose deaths involving both fentanyl and stimulants. This pattern presents specific risks for people at risk for and living with HIV, who have high rates of stimulant use and disproportionate risk of opioid overdose due to unintentional fentanyl use.

**Study objectives:**

This pilot randomized controlled trial evaluates intramuscular naltrexone as a novel biomedical strategy for opioid overdose prevention among people who use stimulants living with or at risk for HIV. The primary outcome is acceptability; secondary outcomes include effectiveness and safety; and an exploratory outcome characterizes patterns of opioid exposure among people reporting only stimulant use.

**Intervention design:**

: The NOD (Naltrexone for Overdose Prevention) Study will randomize 100 participants 1:1 to receive intramuscular naltrexone (380 mg) every 4 weeks or usual care for 24 weeks. Both arms will receive harm reduction services for overdose prevention including intranasal naloxone and safer consumption supplies.

**Methods:**

Acceptability (primary outcome) will be assessed quantitatively through retention at 24 weeks and proportion of on-time injections, and qualitatively through in-depth interviews (*n* = 35). Effectiveness (secondary outcome) includes incident opioid overdose events requiring medical attention or community naloxone. Safety includes grade 2 or higher adverse events. Opioid exposure patterns (exploratory outcome) will be assessed through monthly urine toxicology, hair samples analyzed via liquid chromatography/mass spectrometry, and Timeline Followback interviews. Analysis will use Kaplan-Meier methods for time-to-event outcomes and mixed methods for implementation evaluation.

**Discussion:**

This study leverages the concept of HIV pre-exposure prophylaxis to the prevention of overdose by evaluating the viability of naltrexone as protection against opioid overdose. Success would demonstrate acceptability of long-acting opioid overdose prevention in people who use stimulants, while providing critical insights into implementation and impact of naltrexone as overdose prevention, as well as evaluating patterns of unintentional opioid use.

## Introduction

The epidemiology of drug-related mortality in the United States has undergone a dramatic transformation, marked by a rise in overdose deaths involving both fentanyl and stimulants. From 2010 to 2021, the proportion of overdose deaths involving both fentanyl and stimulants like methamphetamine increased 60-fold [1]. In San Francisco, over 40% of medically-attended nonfatal opioid overdose events occurred among people who reported no intentional opioid use, with most intending to use only stimulants [2]. Unintentional opioid use may result from fentanyl contamination of stimulants, accidental use of fentanyl given its similar appearance to stimulants, or use of cross-contaminated smoking equipment. This pattern of unintentional fentanyl use presents a critical challenge to existing overdose prevention strategies.

People living with HIV (PWH) and those at risk for HIV infection face heightened vulnerability in this evolving crisis. Stimulant use is highly prevalent, with methamphetamine and cocaine use rates ranging from 15 to 30% in general HIV cohorts and exceeding 80% in a cohort of PWH experiencing homelessness [3–5]. Although PWH have had historically lower rates of opioid use disorder (as compared to other substance use disorders), life expectancy among PWH in some regions has decreased related to the overdose crisis, suggesting unintentional fentanyl use could be playing a role [4, 6]. The analysis of substances in hair is emerging as a powerful biomarker to either detect or quantify patterns of substance use over time [7, 8]. Recent biomarker studies by our group using hair analyses demonstrated that 22% of gay men and other men who have sex with men at risk for HIV or living with HIV had hair samples positive for fentanyl, despite denying opioid use [9]. 

Current overdose prevention strategies demonstrate significant limitations in addressing unintentional fentanyl use. While community drug checking services and fentanyl test strips offer some protection, legal and implementation barriers and technical limitations restrict their protective potential [10, 11]. Traditional interventions such as opioid agonist treatments effectively prevent overdose in people with opioid use disorder, but are not appropriate for individuals exclusively using stimulants. The increasing number of overdose deaths related to both fentanyl and stimulants creates an urgent need for novel prevention approaches.

Naltrexone, an opioid receptor antagonist with an established safety profile in treating alcohol and opioid use disorders, represents a potential but unexplored tool for overdose prevention in this context [12]. Naltrexone functions as a competitive antagonist at µ-opioid receptors, the primary site of action for fentanyl’s respiratory depressant effects. By occupying these receptors with high affinity and long duration (approximately 4 weeks for the long-acting formulation), naltrexone prevents fentanyl from binding and exerting its potentially fatal respiratory depressant effects [13]. This mechanism may be particularly relevant for opioid-naïve individuals who lack tolerance to opioid-induced respiratory depression, in which small amounts of inadvertent fentanyl could result in fatal overdose. While the role of naltrexone in addiction treatment is well-documented, its potential as a preventive intervention for people who use stimulants at risk of unintentional opioid exposure remains unstudied. Monthly intramuscular naltrexone could offer a novel biomedical approach to overdose prevention, particularly valuable for PWH and others who use stimulants but do not intentionally use opioids and lack opioid tolerance. This approach aligns with lessons learned from HIV prevention, where long-acting interventions have proven more effective than those requiring daily adherence or point-of-use decision-making [14]. However, risks and benefits of this approach are unknown (Fig. 1).

**Fig. 1 Fig1:**
[figure not shown]
NOD study measures & procedures

### NOD study objectives

The Naltrexone for Overdose Prevention (NOD) study is a pilot randomized controlled trial designed to evaluate intramuscular naltrexone as a novel biomedical strategy for opioid overdose prevention among people who use stimulants living with or at risk for HIV, with the following outcomes:

The primary outcome is acceptability of intramuscular naltrexone as opioid overdose prevention, assessed quantitatively by retention at 24 weeks and proportion of on-time injections, and qualitatively through sequential explanatory in-depth interviews.Secondary outcomes include: (A) effectiveness, evaluated by incident opioid overdose events and (B) safety.An exploratory objective is to characterize patterns of opioid exposure using both short-term (urine) and long-term (hair) biomarkers among people who report stimulant use without intentional opioid use, providing insight into the scope and frequency of unintentional fentanyl exposure in this population.

## Methods

### NOD study design

This 24-week pilot randomized controlled trial will evaluate intramuscular naltrexone for opioid overdose prevention among individuals living with or at risk for HIV who use stimulants. The study will enroll 100 participants randomized 1:1 to receive either monthly intramuscular naltrexone (380 mg) or usual care, and both groups will receive harm reduction services.

#### Study setting and population

The study will be conducted at the San Francisco Department of Public Health, with targeted recruitment from HIV prevention and treatment settings. Eligible participants must: (1) be living with HIV or at risk for HIV through condomless serodiscordant or unknown sex or shared injection equipment, (2) use cocaine or methamphetamine at least 10 days per month AND either meet criteria for stimulant use disorder *or* have positive urine toxicology testing for methamphetamine or cocaine in past 6 months, (3) be English-speaking, and (4) be 18 years or older. We will *exclude* individuals with any prescribed or non-prescribed opioid use, use of extended-release naltrexone within the prior 30 days, planned surgery in the next six months, moderate to severe liver disease, pregnancy or breastfeeding, bleeding risk, or naltrexone hypersensitivity.

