#### Baseline assessments

At screening, participants will undergo comprehensive evaluation including medical history, physical examination, and DSM-V assessment for substance use disorders [15]. Laboratory testing will include complete blood count, comprehensive metabolic panel, and HIV testing for those reporting HIV-negative status. For participants who report living with HIV, status will be confirmed through medical records or documentation. Prior to enrollment, participants will complete informed consent that includes detailed discussion of randomization, medical risks and medical record review, and education regarding the investigational nature of naltrexone for overdose prevention.

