#### Follow-up assessments

Monthly follow-up visits will include clinical assessment, adverse event monitoring, and collection of biomarkers. At weeks 12 and 24, participants will undergo additional laboratory testing including complete blood count and comprehensive metabolic panels. All participants, regardless of study completion or early discontinuation, will be offered assistance to receive provider-prescribed naltrexone at study conclusion which is possible via public insurance in California. A final assessment at week 32 will evaluate incident overdoses and adverse events via telephone interview.

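### The naltrexone exclusion covers only the extended-release form, so current users of another formulation can enter usual care and slightly dilute the overdose comparison

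*Protocol article*

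**What the plan says.** Three exclusions under *Study setting and population* could bear on naltrexone:

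- "use of extended-release naltrexone within the prior 30 days", the only one about earlier use of the drug;
- "any prescribed or non-prescribed opioid use";
- "naltrexone hypersensitivity".

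The Introduction describes naltrexone as "an opioid receptor antagonist with an established safety profile in treating alcohol and opioid use disorders". It gives the duration of receptor occupancy as "approximately 4 weeks for the long-acting formulation", which implies that other formulations exist, although the article never names oral naltrexone.

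The comparison is set out under *NOD study design*: "The study will enroll 100 participants randomized 1:1 to receive either monthly intramuscular naltrexone (380 mg) or usual care". Allocation is open to participants and clinicians (*Randomization and blinding*).

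Under *Sample size and power*, the usual-care overdose risk is taken as 12% over 24 weeks against none in the intervention arm. The Discussion says the pilot will supply baseline overdose incidence for powering a definitive trial.

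**The concern.** By naming a washout, the plan treats recent naltrexone as a reason not to enrol someone. It then limits that rule to one formulation. A person who takes another formulation, for instance for alcohol use disorder (which is not an exclusion), passes the criteria as printed. In the intervention arm this does little to the contrast. In usual care it places the study drug's mechanism in the comparator.

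Two results are exposed. The overdose comparison, a secondary outcome, would be pulled toward no difference. The usual-care overdose incidence, which is the only incidence observed without the study injection, would be understated for a population without opioid blockade and would carry that into the next trial's sample size.

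**Working it through.** **Does another criterion or check close the gap?**

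| Provision | Reaches a current user of another formulation? |
|---|---|
| Extended-release use in the last 30 days | No, different formulation |
| Opioid use | No, the Introduction classes naltrexone as an antagonist |
| Hypersensitivity | No, a current user who tolerates the drug passes |
| Urine test before the first injection (*Intervention arm & standard care components*) | No, it looks for opioids and precedes an injection that usual care does not receive |
| Covariates named for the overdose model (*Effectiveness analysis*) | Not named: age, race or ethnicity, housing and HIV status are |

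None does.

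**The plan's own figure.** *Sample size and power* gives 80% power for 4.72 events (12%) against 0. With 50 per arm, 12% is 0.12 × 50 = 6.0 events, whereas 4.72 / 50 = 9.44% and 4.72 / 0.12 = 39.3 participants. The normal approximation with pooled variance at α = 0.05 gives:

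- 12% against 0, 50 per arm: 72.1% two-sided, 81.9% one-sided;
- 9.44% against 0, 50 per arm: 60.7% two-sided, 72.4% one-sided.

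Only 6.0 events with a one-sided test comes close to 80%, and that does not match 4.72. This mismatch is a separate matter. I use 12% of 50 as the base below and give the effect on 4.72 afterwards.

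**Illustration of dilution.** Let f be the share of usual care taking non-study naltrexone, and assume it protects fully. Control risk is then 0.12 × (1 − f), and expected events are 50 times that. Neither f nor full protection comes from the article; both are assumptions.

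| f | Control risk | Expected events | Power, two-sided | Power, one-sided |
|---|---|---|---|---|
| 0% | 12.0% | 6.0 | 72.1% | 81.9% |
| 5% | 11.4% | 5.7 | 69.7% | 79.9% |
| 10% | 10.8% | 5.4 | 67.1% | 77.8% |
| 20% | 9.6% | 4.8 | 61.5% | 73.1% |

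On the printed 4.72 events, the loss is 0.05 × 4.72 = 0.24 events at f = 5% and 0.20 × 4.72 = 0.94 at f = 20%. Protection that is less than complete shrinks every loss in proportion.

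**How fragile are counts this small?** The two-sided Fisher test with 50 per arm gives p = 2 × C(50,6) / C(100,6) = 0.027 for 6 against 0, and p = 2 × C(50,5) / C(100,5) = 0.056 for 5 against 0. One event fewer in usual care crosses 0.05. The expected loss, however, reaches a full event only near the top of the assumed range (6.0 − 4.8 = 1.2 at f = 20%).

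**The case against.** The strongest reply is that this is an article. Concomitant-medication forms and the handling of off-study treatment belong to the full protocol and analysis plan, so their absence proves nothing. That is right about absence. But the article does not leave the criterion out; it prints one and limits it to a single formulation. If the full protocol is wider, the printed wording still needs correcting.

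A second reply is that the stated comparator is usual care, not absence of blockade, and that usual care may include other prescribed treatment. The rate under usual care is then the proper planning figure for a later trial against usual care. This stands in part. It is why intention-to-treat should stay primary and why the incidence should be reported both ways.

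Several stronger readings are tempting, and the article does not support them:

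- *That nothing in the plan could identify such use.* *Implementation analysis* lists concurrent medications among its subgroups, so some medication data are probably collected. They are assigned to attrition, not to overdose. The overdose covariate list is also open-ended, and *Missing data and sensitivity analyses* plans a per-protocol analysis.
- *That usual-care participants are prompted to start naltrexone during the 24 weeks.* The consent discussion covers "education regarding the investigational nature of naltrexone for overdose prevention", which is not teaching that it works. The insurance remark concerns "provider-prescribed naltrexone at study conclusion which is possible via public insurance in California". It shows that the drug can be obtained, not that uptake will occur during treatment. The one period where the study itself may help start it is between that offer and the week-32 call, if the offer precedes the call.
- *That acceptability is flattered.* Retention and on-time injections measure acceptance of a monthly injection. Taking another formulation does not establish that, and recent extended-release users are excluded.
- *That usual-care follow-up should simply be censored when naltrexone starts.* Starting may follow a near miss or a rise in perceived risk, so such censoring could be informative.

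**Conclusion.** The point holds in a limited form. As printed, the criteria admit current users of naltrexone in formulations other than extended-release, and no other printed provision stops them from being allocated to usual care. The direction of bias is toward no difference in overdose and toward a lower baseline incidence.

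The size cannot be derived from the article and is probably small. The range of 5.7 to 4.8 events in place of 6.0 rests on an assumed 5% to 20% exposure and on full protection, and should not be read as an estimate. Effectiveness is a secondary outcome of a pilot for which the article itself says formal power calculations are precluded, and the primary outcome is little affected. The change is worth making because it is cheap and because exposure not recorded during follow-up cannot reliably be recovered later.

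**What to change.** 1. Extend the exclusion to current use of naltrexone in any formulation, keeping the 30-day window for extended-release.
2. Record any non-study naltrexone, with start and stop dates, in both arms at the existing 4-weekly visits and at the week-32 call.
3. Keep intention-to-treat as the primary analysis of overdose.
4. Report usual-care overdose incidence overall and, as a sensitivity result, for person-time without non-study naltrexone. State that starting naltrexone may itself be related to overdose risk, so the second figure is not free of bias.

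The cost is one line in the eligibility criteria, one form item and one extra incidence estimate. The downside is that a few candidates already taking naltrexone would not be enrolled.

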#### Intervention

Participants randomized to the intervention arm will receive monthly intramuscular naltrexone 380 mg administered in the ventrogluteal region. Both intervention and usual care arms will receive standard harm reduction services including naloxone, safer consumption supplies, and fentanyl test strips. All participants will undergo monthly clinical assessments and biomarker collection for the evaluation of substance use throughout the 24-week study period.

#### Randomization and blinding

Following eligibility confirmation and obtaining written informed consent, participants will be randomized 1:1 to either intramuscular naltrexone or usual care using a computer-generated randomization sequence with random block sizes. Participants and clinicians will not be blinded to treatment assignment, but laboratory personnel conducting biomarker analyses will remain blinded to treatment allocation.

#### Baseline assessments

At screening, participants will undergo comprehensive evaluation including medical history, physical examination, and DSM-V assessment for substance use disorders [15]. Laboratory testing will include complete blood count, comprehensive metabolic panel, and HIV testing for those reporting HIV-negative status. For participants who report living with HIV, status will be confirmed through medical records or documentation. Prior to enrollment, participants will complete informed consent that includes detailed discussion of randomization, medical risks and medical record review, and education regarding the investigational nature of naltrexone for overdose prevention.

#### Intervention arm & standard care components

Participants randomized to the intervention arm will receive monthly intramuscular naltrexone (380 mg) administered in the ventrogluteal region. Prior to the initial injection, participants will undergo point-of-care urine testing to confirm absence of opioids and prevent precipitated withdrawal. For participants with positive fentanyl testing who deny intentional use, or in cases of clinical uncertainty regarding unintentional exposure, we offer an intranasal naloxone challenge before long-acting naltrexone administration. The choice of ventrogluteal injection site is based on previous research suggesting better tolerability at this site compared to dorsogluteal administration [16]. Both intervention and usual care arms will receive harm reduction supplies. This includes intranasal naloxone (4 mg, two doses), participant-selected safer consumption supplies tailored to route of administration, and fentanyl test strips with instructions to minimize false positives.

#### Study visits and clinical monitoring

Following enrollment, participants attend study visits every 4 weeks through week 24, compensated $50 per visit. Each visit includes a symptom-driven physical examination, vital signs monitoring, and adverse event assessment. Laboratory monitoring includes complete blood count and comprehensive metabolic panel at weeks 12 and 24.

#### Post-study transition

At study conclusion, all participants, including those who discontinue early, will be offered assistance in receiving provider-prescribed naltrexone through their primary care providers. For participants receiving HIV care at San Francisco General Hospital’s Ward 86 clinic who are on long-acting injectable antiretroviral therapy, we offer coordination of naltrexone administration with their routine HIV care visits. This ensures continuity of care beyond the study period for participants who find the intervention beneficial.

#### Protocol modifications and discontinuation

The protocol includes specific criteria for individual participant discontinuation and study-wide stopping rules. Individual discontinuation may occur due to participant request, unacceptable toxicity, or need for full-agonist opioids. Study-wide stopping rules include observation of unanticipated adverse effects or emergence of new safety information. In addition to the UCSF Institutional Review Board, the UCLA Data Safety Monitoring Board reviews all serious adverse events and provides recommendations annually regarding study continuation.

### Assessment & data collection

#### Overview

The study will assess outcomes across three categories, aligned with our primary, seconday, and exploratory objectives. The primary outcome is acceptability of intramuscular naltrexone, evaluated through both quantitative implementation metrics and qualitative interviews with participants in both arms. Secondary outcomes include effectiveness (incident opioid overdose events requiring medical attention or community naloxone administration) and and safety including grade 2 or higher adverse events. The exploratory outcome characterizes patterns of opioid exposure via monthly point-of-care urine toxicology, hair analysis for substance exposure via liquid chromatography-tandem mass spectrometry (LC-MS/MS)-based methods, and Timeline Followback interviews [17]. 

#### Primary outcome: acceptability

The primary outcome is acceptability of intramuscular naltrexone as opioid overdose prevention, assessed through both quantitative and qualitative measures. Quantitatively, we will evaluate the following implementation outcomes: (1) the proportion of participants recruited versus enrolled, (2) time to goal enrollment, (3) number of visits completed per participant, (4) retention in treatment at 24 weeks, and (5) the proportion of on-time injections during the study period. We will consider 50% of enrolled participants completing 3 or more injections the minimum standard for adequate intervention uptake.

For qualitative evaluation, we will conduct sequential explanatory in-depth interviews with up to 35 individuals purposively sampled across levels of engagement, including participants from both study arms and eligible individuals who declined participation. This sample size was strategically chosen to ensure comprehensive thematic saturation while capturing a broad spectrum of participant experiences with long-acting injectable naltrexone as an overdose prevention strategy. The interviews will explore multiple dimensions, including general acceptability factors like intervention burden and perceived effectiveness; intramuscular naltrexone-specific factors, addressing subjective experiences of ongoing substance use, risk compensation, and trust in long-acting injectable medications; and HIV-specific factors, including experiences with multiple injectable medications for HIV and SUDs. Additional topics include perceived frequency of unintentional opioid exposure among people using stimulants, proposed mechanisms of exposure, and views on harm reduction strategies.

